## Abstract

**Background:**

A strong association exists between sleep duration and glycemic control in patients with type 2 diabetes (T2D), yet convincing evidence of a causal link remains lacking. Improving sleep is increasingly emphasized in clinical T2D treatment guidance, highlighting the need for effective, scalable sleep interventions that can affordably serve large populations through mobile health (mHealth).

**Objective:**

This study aims to pilot an intervention that extends sleep duration by modifying bedtime behavior, assessing its efficacy among short-sleeping (≤6 hours per night) patients with T2D, and establishing robust evidence that extending sleep improves glycemic control.

**Methods:**

This randomized, single-blinded, multicenter study targets 70 patients with T2D from 9 institutions in Japan over a 12-week intervention period. The sleep extension intervention, BedTime, is developed using the Theory of Planned Behavior (TPB) and focuses on TPB’s constructs of perceived and actual behavioral control (ABC). The pilot intervention combines wearable actigraphy devices with SMS text messaging managed by human operators. Both the intervention and control groups will use an actigraphy device to record bedtime, sleep duration, and step count, while time in bed (TIB) will be assessed via sleep diaries. In addition, the intervention group will receive weekly bedtime goals, daily feedback on their bedtime performance relative to those goals, identify personal barriers to an earlier bedtime, and select strategies to overcome these barriers. The 12-week intervention period will be followed by a 12-week observational period to assess the sustainability of the intervention’s effects. The primary outcome is the between-group difference in the change in hemoglobin A_1c_ (HbA_1c_) at 12 weeks. Secondary outcomes include other health measures, sleep metrics (bedtime, TIB, sleep duration, total sleep time, and sleep quality), behavioral changes, and assessments of the intervention’s usability. The trial commenced on February 8, 2024, and is expected to conclude in February 2025.

**Results:**

Patient recruitment ended on August 29, 2024, with 70 participants enrolled. The intervention period concluded on December 6, 2024, and the observation period ended on February 26, 2025, with 70 participants completing the observation period. The data analysis is currently underway, and results are expected to be published in July 2025.

**Conclusions:**

This trial will provide important evidence on the causal link between increased sleep duration and improved glycemic control in short-sleeping patients with T2D. It will also evaluate the efficacy of our bedtime behavior change intervention in extending sleep duration, initially piloted with human operators, with the goal of future implementation via an mHealth smartphone app. If proven effective, this intervention could be a key step toward integrating sleep-focused mHealth into the standard treatment for patients with T2D in Japan.

**Trial Registration:**

Japan Registry of Clinical Trials jRCT1030230650; https://jrct.niph.go.jp/latest-detail/jRCT1030230650

**International Registered Report Identifier (IRRID):**

DERR1-10.2196/64023

## Introduction

Worldwide, approximately 537 million people aged 20-79 years have diabetes [1]. Diabetes is a serious public health concern, significantly impacting health care expenditures and human life, causing 4.2 million deaths annually [2,3]. Type 2 diabetes (T2D) is difficult to cure once it develops and, if left untreated, can lead to complications such as cardiovascular disease and microvascular damage [4].

T2D treatment guidelines include both pharmacological and lifestyle modification elements. Traditionally, lifestyle modifications have focused on diet and exercise, but recently, improving sleep in patients with T2D has gained prominence [5,6]. Some patients with T2D suffer from sleep disorders, including obstructive sleep apnea, restless leg syndrome, and insomnia, for which treating the underlying disorder is the appropriate approach [7]. Sleep quality is associated with T2D risk [8], and interventions to improve sleep quality have shown effectiveness [9]. Many patients with T2D do not get sufficient sleep, experiencing what is termed *short sleep*. Definitions of short sleep vary across studies, ranging from 6 or fewer hours per night to less than 4.5 hours per night [10]. This issue is widespread, with data indicating that 39.4% of patients with T2D in Japan sleep fewer than 6.4 hours per night [11].

There is strong evidence that short sleep is associated with an increased risk of T2D and poorer glycemic control. In Japanese patients with T2D, short sleep is linked to higher hemoglobin A_1c_ (HbA_1c_) levels [11], with a meta-analysis indicating a 0.23% difference in HbA_1c_ due to short sleep [12]. Prospective studies have also shown an increased risk of T2D associated with short sleep [8]. Plausible biological mechanisms support these findings, as sleep extension has been shown to reduce energy intake [13], while sleep restriction worsens insulin sensitivity [14].

Surprisingly, there is a lack of strong evidence for causality—specifically, increasing sleep duration in short-sleeping patients with T2D without sleep disorders leads to improvements in HbA_1c_ levels. Recent meta-analyses [15,16] found limited and conflicting evidence on the effect of sleep interventions on glycemic control. Some studies have investigated interventions for patients with T2D with insomnia [17,18]. One study examined an educational intervention for patients with T2D, including those with short sleep, but results from a published abstract [19] are unclear, and no full paper has been published. Two related studies used cognitive behavioral therapy to improve HbA_1c_ by enhancing sleep quality rather than duration [20,21]. Overall, strong evidence is lacking to support the idea that increasing sleep duration in short-sleeping patients with T2D without sleep disorders leads to improved HbA_1c_ levels.

Numerous studies have successfully increased sleep duration in various populations. A recent meta-analysis of 42 studies found that extending time in bed (TIB) has the greatest potential to modify sleep, with direct interventions (ie, scheduling a longer period in bed) resulting in an average increase of 1 hour and 23 minutes in sleep duration [22].

Mobile health (mHealth) interventions, such as mobile phone apps supporting self-management, have been shown to be effective in increasing physical activity, reducing body weight [23,24], and improving glycemic control [25,26]. However, to our knowledge, no mHealth apps have been designed specifically to improve sleep duration in short-sleeping patients with T2D without sleep disorders. Personalization of intervention components has been shown to enhance patient motivation and engagement with the app [27]. Several studies have found that tailored interventions are more effective at changing health behaviors than nontailored ones [28,29]. Moreover, interventions based on behavior change theory have been shown to be more effective than those lacking a theoretical foundation [30], with those based on the Theory of Planned Behavior (TPB) being particularly effective [31]. TPB emphasizes intention and ABC as key determinants of behavior, with perceived behavioral control (PBC)—similar or identical to Bandura’s self-efficacy—playing a central role in shaping intention [32,33].

To address the lack of evidence on whether improvements in sleep duration lead to better glycemic control, we developed a pilot study of a personalized mHealth intervention, BedTime, designed to increase sleep duration and assess its impact on glycemic control in short-sleeping patients with T2D. The intervention is based on the TPB framework to promote behavior change toward earlier bedtimes. This trial aims to evaluate the efficacy of the BedTime approach in a 12-week, single-blind, randomized controlled pilot trial. The specific research objectives and hypotheses are as follows:

Objective 1: To evaluate the efficacy of the BedTime approach in shifting patients to an earlier bedtime, as measured by daily bedtime reporting, and increasing sleep duration, as measured by daily actigraphy.We hypothesize that, by the end of the intervention, the intervention group will show statistically significant changes in bedtime and sleep duration compared with the control group.Objective 2: To evaluate the efficacy of the BedTime approach in reducing HbA_1c_ levels.We hypothesize that, by the end of the intervention, the intervention group will show a statistically significant reduction in HbA_1c_ levels compared with the control group.

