### Intervention Design

Some features of the intervention are shared by both the control and intervention groups, while others are unique to the intervention group (Table 1). This mHealth intervention incorporates a physical activity monitoring system (iAide2; Tokai) and a researcher-designed paper diary for patients in both groups. The iAide2 measures activity intensity levels, skin temperature, and pulse rate [34,35] to assess step count and sleep, providing minute-by-minute wake/sleep assessments [36,37]. Additionally, the iAide2 enables timely behavioral feedback via a wirelessly connected Event button and near-real-time data access for researchers through an administrative screen. During the 12-week intervention period, patients in both the control and intervention groups wear the iAide2 device at all times except when bathing and press its Event button at bedtime each day. Patients record their bedtime and risetime daily in the paper diary. For the intervention group, the diary includes additional pages implementing specific aspects of the intervention. Bedtime is defined as the time when a patient begins trying to sleep, and risetime as the time when they stop trying to sleep. Diary entries are used to calculate TIB, the duration between bedtime and risetime. The intervention is designed to encourage an earlier bedtime, with the expectation that this will extend TIB and thereby increase sleep duration (ie, the portion of the TIB interval during which the patient is asleep).

**Table 1 table1:** Intervention features for the intervention and control groups.

Features			Intervention group		Control group

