**SMS text message**					
	Diary reminder	Yes		Yes	
	Low battery message	Yes		Yes	
	Daily feedback and target bedtime	Yes		No	
	Request for a reply message when patients forget to press the Event button	Yes		No	

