### Intervention Process

The study (Table 4) consists of 5 events (E0-E4), a 2-week run-in period, a 12-week intervention period, and a 12-week observation period. Initial measurements will be taken at event E0. Questionnaires will be used to assess sleep behavior and gather patient feedback (Textbox 5).

Following randomization, the intervention begins. Before explaining the intervention, the researcher or CRC will administer the TPB Sleep Questionnaire and the Sleep-Related Behavior (SRB) Questionnaire to the intervention group. The researcher or CRC will then provide a diary customized for the intervention group. To establish a baseline bedtime, the researcher or CRC will average bedtimes recorded during the run-in period, considering any exclusions due to unusual circumstances in consultation with the patient. Patients will be informed that their ultimate goal is to shift their bedtime 1 hour earlier than the baseline, with an initial target of going to bed 10 minutes earlier during the first week. The researcher or CRC will help patients identify barriers preventing them from going to bed early and assist them in selecting up to 3 coping strategies tailored to these barriers for the first week. During this process, the researcher or CRC will facilitate discussions using the list in the diary as a reference. Patients may either choose strategies from the list or write their own in the diary. For the control group, the researcher or CRC will provide a diary similar to the one used during the run-in period but covering 12 weeks. Control group patients will be instructed to continue recording their bedtime and risetime as they did during the run-in period. The intervention period lasts 12 weeks, from E1 to E3. We will send reminder SMS text messages to both groups at the end of weeks 1 and 10 to encourage diary use. All equipment, including the diary, will be collected at E3 before the follow-up observation period begins.

For the intervention group, we will provide both daily and weekly feedback. Researchers will monitor the receipt of the Event time, and if it is missing, they will send a reminder asking the patient to report their bedtime via an SMS text message. If no bedtime is reported through either the Event record or SMS text message, the night will be considered a failure to achieve the target bedtime. At E2, 10 weeks after E1, we will send a reminder for participants to complete the TPB Sleep Questionnaire in the diary.

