#### Secondary Outcomes

Secondary outcomes (Table 5) include health measures, bedtime and sleep measurements, other behavior change assessments, and evaluations of actigraph and diary usage. We will also assess safety outcomes, including hypertension requiring medical assistance (evaluated from system records), subjective hypoglycemia, lower back pain, and pain in the lower extremities (tarsus, thighs, knees, calves, shins, ankles, and feet), as well as any other adverse events (all assessed through patient interviews).

**Table 5 table5:** Secondary outcomes investigated in the study.

Measurements	Outcomes
Differences in changes	Hemoglobin A_1c_ (%) (only after the end of the observation period)^a^ Weight (kg)^a^ BMI (kg/m^2^)^a^ Systolic blood pressure/diastolic blood pressure (mmHg)^a^ Estimated glomerular filtration rate (mL/min/1.73 m2)^a^ Fasting blood sugar (mg/dL)^a^ Low-density lipoprotein cholesterol (mg/dL)^a^ High-density lipoprotein cholesterol (mg/dL)^a^ Neutral fat (mg/dL)^a^ Urine albumin-to-creatinine ratio (mg/gCr)^a^ PSQI-J^a,^^b^
Differences in the measured values	Survey on past bedtimes^a^
Difference in proportions	Behavior change questionnaire^a^
Observed data	Elements of the bedtime questionnaire: attitude, subjective norms, perceived behavioral control, intention^c^ Sleep time calculated from iAide2’s sleep data and diary data^d^ Time in bed calculated from bedtime and wake-up time recorded in the diary for each period^d^ Bedtime recorded in the diary for each period and bedtime sent from iAide^d^ Steps recorded by iAide2^d^ Achievement rate of target bedtime^e^ Number of barriers and coping strategies set and implemented in the diary for the intervention period^e^ Percentage of use of each drug^f^ Percentage of new additions for each drug since consent was obtained^g^ Changes in antidiabetic drugs since consent was obtained (strengthened, unchanged, or attenuated)^g^

^a^Evaluate the differences after the end of the intervention period (at 12 weeks) and after the end of the observation period (at 24 weeks) from the time of consent acquisition.

^b^PSQI-J: Pittsburgh Sleep Quality Index, Japanese version.

^c^Evaluate the differences in the measured values for the following items at 10 weeks and after the end of the observation period (24 weeks).

^d^Evaluate the differences in the average change from the trial period in the 2 weeks before the end of the intervention period.

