## Discussion

We designed this study based on the foundational concept that it is a behavioral change intervention, despite measuring medical outcomes. The intervention is grounded in a specific theory of behavioral change (TPB) to provide a structured framework, ensure clarity on intervention targets, and maintain focus, avoiding a scattershot approach. We identified a specific, actionable target behavior—going to bed earlier—and developed a measurement and feedback system centered on this behavior. This focused approach provides clarity for both researchers and patients. By maintaining this focus, we can determine whether the intervention effectively changes sleep behavior while also evaluating its impact on sleep patterns and, ultimately, health outcomes. Demonstrating that a behavioral intervention improves HbA_1c_ is not enough, we need to understand the intermediate steps, particularly the behavioral response, to refine the intervention by enhancing effective components and eliminating ineffective ones. This study is designed to generate evidence on these intermediate stages.

Our study utilizes objectively measured data for all primary outcomes and many secondary outcomes. The intervention leverages wireless technology, enabling automatic synchronization of sleep and step count data to the server. These simple, passive features facilitate easy-to-use objective measurements, particularly for older patients.

Participants will be blinded to group assignments to minimize social desirability bias. To achieve this, they will not be informed that the study involves random assignment to 2 groups or that the intervention specifically targets advancing bedtime. Instead, patients will be told that the study examines the relationship between self-management of lifestyle habits (including exercise and sleep) and blood glucose control in individuals with T2D. They will also be informed that various lifestyle factors, including sleep, will be monitored. This approach minimizes the risk of unblinding in the control group by preventing participants from identifying the absence of an intervention. We believe that maintaining blinding offers significant scientific benefits by reducing potential bias and enhancing the validity of the study findings.

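### Objective 1's bedtime outcome is patient-reported and graded daily in the intervention arm only, and the stated blinding cannot protect that arm from reporting bias

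*Protocol article*

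**What the plan says.** The Introduction states Objective 1 as "shifting patients to an earlier bedtime, as measured by daily bedtime reporting" and "increasing sleep duration, as measured by daily actigraphy". It hypothesises that "the intervention group will show statistically significant changes in bedtime and sleep duration compared with the control group".

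- **Source of bedtime.** Under Intervention Design, patients in both arms "press its Event button at bedtime each day" and also write bedtime and risetime in a paper diary. Bedtime is defined as the moment the patient starts trying to sleep. Table 5 takes the bedtime outcome from the diary and from the time sent by the device, and time in bed (TIB) from the diary alone. Footnote d compares the last 2 weeks of the intervention with the trial period, which the E1 exclusion criteria show to be the run-in.
- **Source of sleep duration.** Table 5 lists "Sleep time calculated from iAide2’s sleep data and diary data". Intervention Design defines sleep duration as the part of TIB spent asleep, and says the iAide2 classifies each minute as wake or sleep.
- **Differences between arms.** Table 1 gives the intervention arm alone a target bedtime, daily feedback, and "Request for a reply message when patients forget to press the Event button". Intervention Process adds that a night with no bedtime from either the Event record or a text reply counts as a failure. Study Overview confirms that controls get neither feedback nor goals.
- **What patients know.** Intervention Process: "Patients will be informed that their ultimate goal is to shift their bedtime 1 hour earlier than the baseline". The Discussion, explaining how social desirability bias is limited, says "they will not be informed that the study involves random assignment to 2 groups or that the intervention specifically targets advancing bedtime".

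**The concern.** In the intervention arm, the Event press is both an outcome measurement and the thing on which the patient is praised or told that the target was missed. In the control arm it is only a measurement. Patients who know the target and are assessed against it each day have a reason to press, or to write, a somewhat earlier time than the true one. Controls have no such reason. A baseline-adjusted comparison cannot remove this, because the incentive starts after the run-in and in one arm only.

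The safeguard named in the Discussion is ignorance of the bedtime target. That ignorance is absent in the arm where the bias would arise. What is at stake is whether an observed difference in bedtime and TIB can be read as a change in behaviour. The Discussion itself says that an HbA1c improvement is not sufficient without understanding the behavioural steps that lead to it.

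**Working it through.** **1. The plan's own figure.** The only sample-size calculation is for HbA1c (difference 0.3, SD 0.41, two-sided 0.05, power 80%). The normal approximation is 2 × (1.96 + 0.842)² × (0.41/0.3)² = 29.3, so 30 per group. The t-based solution is 30.3, so 31, as stated. 31/0.9 = 34.4, so 35 per group and 70 in total. It reproduces and is not at issue. It supplies the 35 per arm used below.

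**2. Which measure is exposed, and how.**

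| Measure | Source | Patient-generated? | Graded daily in one arm? |
|---|---|---|---|
| Bedtime, Event | button press | yes | yes |
| Bedtime, diary | paper entry | yes | not directly |
| TIB | diary bedtime and risetime | yes | not directly |
| Sleep duration | iAide2 minutes, with diary | in part | no |
| HbA1c | laboratory | no | no |

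Grading and chasing attach to the Event time or the text reply. The paper diary is collected at E3. Diary bedtime and TIB are therefore exposed through knowledge of the target and a wish to be consistent with the press, not through daily assessment of the entry.

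**3. Size relative to the target.** Inputs from the article are a first-week target of 10 minutes, an ultimate goal of 60 minutes, and weekly increases of 5, 10 or 15 minutes. I assume a constant weekly increase, capped at 60.

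- +5 per week: week 11 is 10 + 10 × 5 = 60; week 12 is held at 60.
- +15 per week: 10, 25, 40, 55, then 60 from week 5.

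Both paths stand at 60 in weeks 11 and 12, the window of footnote d. An assumed 10-minute reporting shift is 10/60 = 17% of that target. The algorithm also allows decreases, so a patient whose target is still below 60 would give a larger share.

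**4. Effect on the test of bedtime.** The article gives no SD for change in bedtime, so I assume 30 to 60 minutes. With no true effect and a one-arm reporting shift b, SE = SD × √(2/35), and the false-positive rate is 1 − Φ(1.96 − b/SE) + Φ(−1.96 − b/SE).

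| SD (min) | SE | Smallest significant difference | Rate, b = 10 | Rate, b = 15 |
|---|---|---|---|---|
| 30 | 7.2 | 14 min | 29% | 55% |
| 45 | 10.8 | 21 min | 15% | 29% |
| 60 | 14.3 | 28 min | 11% | 18% |

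**5. Effect on sleep duration.** A falsely early diary bedtime widens the window, but only minutes that the device scores as sleep add to the outcome. Assume that 10% to 50% of the extra window is so scored. A 10-minute shift then adds 1 to 5 minutes, with false-positive rates of 5% to 11% over the same SDs. A 20-minute shift adds 2 to 10 minutes, with rates of 5% to 29%. The exposure is real but diluted.

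**The case against.** The case on the other side is substantial.

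- **Grading is not on the diary.** Correct. The documents do not support a direct chain from daily assessment to diary entry to sleep time.
- **Texted bedtimes are not listed as a between-group outcome.** Correct. Table 5 names the diary and the device. The documented use of text replies is to judge target achievement, an intervention-only measure that needs them. The one-sided chase may still affect how consistently patients press the button.
- **Sleep duration by actigraphy and by device plus diary are compatible.** Largely correct. The diary appears to enter only as the TIB window, and an article may leave the algorithm to the full protocol.
- **The two statements on blinding may refer to different times.** The Discussion may describe what patients are told at consent, and it speaks of avoiding unblinding in the control group. That would ease the contradiction. It would not protect the intervention arm while outcomes are being recorded.
- **Feedback is the intervention and cannot be balanced.** True, and the device, the bedtime and risetime fields and the diary reminders are the same in both arms. That equalises recording, not the incentive attached to it.
- **Sleep onset is not bedtime.** True. This is a reason to add a device measure, not to replace the reported one.

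A reader might infer that Objective 1 could be met through early presses alone. The hypothesis names bedtime and sleep duration together, so the documents do not support that. A reader might also infer that the sleep-to-HbA1c analysis is distorted. No such model is stated; the only exploratory regression uses coping strategies.

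**Conclusion.** The point holds for bedtime and TIB. Both are patient-generated, the Event press is graded and chased in one arm, and the stated blinding protects only the controls. Sleep duration is exposed to a lesser degree. The primary outcome is not exposed to this bias.

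The documents show an incentive, not misreporting. The 17% rests on an assumed 10-minute shift and assumed goal schedules. The false-positive rates rest on assumed SDs and 35 per arm. They show that a shift no larger than the first week's target could matter to a test of bedtime, and they are not estimates of bias in this trial. What must be corrected whatever the size is the claim that blinding limits social desirability bias, because it does not apply to the arm where that bias would arise.

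**What to change.** 1. Reconcile the Discussion with Intervention Process. State that only controls are unaware of the bedtime target, and do not describe self-reported bedtime and TIB as protected by blinding.
2. Keep reported bedtime as the behavioural outcome. Add a prespecified between-group comparison of iAide2-only sleep onset and sleep duration over the footnote d window, scored by one algorithm in both arms without diary, Event or text-message times, using ANCOVA on the run-in value. Require it to agree before Objective 1 is called met, and define agreement in advance. If sleep data have already been examined by arm, label this analysis post hoc.
3. Report by arm the gap between reported bedtime and the first iAide2 sleep minute, and the number of valid nights. A gap that widens from run-in in the intervention arm only would be consistent with earlier reporting, though also with longer sleep latency.
4. Keep texted bedtimes out of the between-group bedtime outcome, and retain them for the intervention-only achievement rate.

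The cost is re-scoring data already collected, plus a few sentences of text. Table 1 says that patients are not shown the device sleep data, so no feedback is based on them. The downside is that sleep onset includes sleep latency and so is not identical to bedtime. The article also does not show how the device would mark out the night's sleep without diary bounds, so that rule must be written down and applied identically in both arms.
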